#### Non-Date Values

There will be no imputation of missing efficacy or safety data. However, the potential influence of rescue or intraoperative nerve blocks, delayed extubation, return to OR and death on MME efficacy endpoints will be explored in sensitivity analyses, described below.

### 3.1.7 Laboratory Values Above or Below Limits of Quantification

For laboratory values less than the lower limit of quantification (LLQ), half of the lower limit value (i.e., LLQ/2) will be used in the analysis. For values greater than the upper limit of quantification (ULQ), the upper limit value (i.e., ULQ) will be used in the analyses.

## 3.2 Analysis Populations

### 3.2.1 Modified Intent-to-Treat (mITT) Population

The mITT Population will include all randomized participants in whom a block catheter was placed, and a dose of study treatment was administered. Treatment classification will be based on the randomized treatment assignment. The mITT Population will be the primary population used for the efficacy analyses.

### 3.2.2 *Safety Population*

The Safety Population will include all participants in whom a block catheter was placed, and a dose of study treatment was administered. Treatment classification will be based on the actual study treatment received. The Safety Population will be the primary population used for safety analyses.

## 3.3 Subject Data and Study Conduct

### 3.3.1 *Subject Disposition*

Counts and percentages of participants who were randomized, completed the treatment period, discontinued treatment (including primary reason for discontinuation), completed the study, and prematurely discontinued from the study (including primary reason for discontinuation) will be summarized by treatment group.

### 3.3.2 *Analysis Populations*

Counts of participants in each analysis population will be summarized by treatment group.

### 3.3.3 *Demographic and Baseline Characteristics*

The following demographic and baseline characteristics will be summarized with descriptive statistics or counts and percentages of participants as appropriate by treatment group for the mITT Population:

- Site of enrollment
- Sex
- Age
- Race/Ethnicity
- Height
- Weight
- Body Mass Index (BMI)
- History of each of the following: coronary artery disease, valvular heart disease, diabetes, hypertension, dyslipidemia, obesity, smoking within past 6 months
- Medications: as collected in the CRF
- Laboratory assessments: as collected in the CRF
- Preoperative cardiac assessment: as collected in the CRF
- PROMIS-29

### 3.3.4 *Concomitant Medications*

Concomitant Medications – other than those included in the efficacy analyses – will be summarized by treatment group for the mITT Population. Intraoperative MMEs will also be summarized.

## 3.4 Efficacy Assessment

The mITT Population will be the primary population for the efficacy analysis.

### 3.4.1 *Primary Efficacy Endpoints*

#### Primary Analysis

The primary efficacy endpoint is the cumulative postoperative opioid use measured as MMEs during the 72 hours following catheter insertion. The conversion of different opioids into MMEs will utilize the table provided in the study protocol.

Administered opioids are documented in the CRF on a daily basis; i.e., the date and time of each administered drug is not recorded. In contrast, the date and time of catheter insertion is recorded in the CRF. Consequently, opioid use for each participant will include those that were administered:

- The day of catheter administration
- The two days following the day of catheter administration
- A fraction of the third day following the day of catheter administration. The fraction will depend on the time of day that the catheter was inserted at the beginning of the 72 hour time interval. For example, if 40 MMEs were administered on the 3rd day and the catheter was inserted at 9:00 AM on day 0, the MMEs on the third day that will be included in the primary efficacy analysis would be  $(9/24) \times 40 = 15$  MMEs.

To assess the primary efficacy endpoint, the primary estimand is defined by the following key attributes:

- **Treatment:** 0.2% ropivacaine versus placebo
- **Target Population:** participants who are randomized into the study and received any amount of study treatment
- **Analysis Population:** The mITT Population
- **Intercurrent events:** premature treatment discontinuation, rescue nerve block, death
- **Analysis set and handling of intercurrent events:** Treatment policy strategy will be used. All available MME values during the 72 hours following catheter insertion will be used in the calculation of cumulative postoperative opioid use
- **Population level summary:** The difference in LS mean cumulative postoperative opioid use during the 72 hours following catheter insertion between treatment groups

The analysis of covariance (ANCOVA) model with a fixed effects for treatment group, sex, BMI and intraoperative MMEs ( $<$ median,  $\geq$ median) will be used to analyze the primary efficacy endpoint. The least squares (LS) mean, standard errors, and 2-sided 95% confidence intervals (CIs) for each treatment group and for the mean difference compared to placebo will be estimated. The model will be fit assuming unequal variances for each treatment group. If substantial deviations from the model assumptions are observed, then supportive analyses, such as robust regression, non-parametric analyses, etc. will be considered. Missing values of predictors will either be imputed by the overall mean or most frequent category.

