| Study Intervention    | Subjects will be randomized (1:1) to receive superficial parasternal intercostal plane block with ropivacaine via ultrasound-guided catheter placement or sham block with saline. Catheters will be inserted into the superficial parasternal intercostal plane bilaterally under ultrasound guidance after skin closure. Following initial bolus dosing at the time of catheter placement, a continuous infusion with intermittent boluses every 3-4 hours of 0.2% ropivacaine, or equivalent volume of 0.9% normal saline, will be delivered via catheters for 48 hours post-catheter insertion.                                                                                                                                                                                                                                                                                                                                                                                                                                                                                                                                                                                                                                                                                                                                                                                                                                                                                                                                                                                                                                                                                                                                                                                                                                                                  |

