#### *Hospitalization*

- Cumulative postoperative opioid use measured as Milligram Morphine Equivalent (MME) from catheter insertion until discharge from hospital, obtained via medication administration record (MAR) in patients' health record.
- Median pain score as measured by a standardized numeric rating scale over 72 hours following catheter insertion (measured at rest and with coughing q12hours  $\pm$  2 hours post-catheter insertion). First assessment will be conducted when patient is awake and able to follow commands following extubation, second assessment will be conducted at the first intervention dose following first assessment, and ongoing assessments will be conducted at approximately every 12 hours thereafter.

- Delirium assessed BID for 72 hours following catheter insertion (see above criteria). First assessment will be conducted when patient is awake and able to follow commands following extubation, second assessment will be conducted at the first intervention dose following first assessment, and ongoing assessments will be conducted at approximately every 12 hours thereafter.
- Time from catheter insertion to extubation
- Time from catheter insertion to first opioid analgesic provision following extubation
- Time from catheter insertion to mobilization
- ICU and hospital LOS
- Postoperative nausea and vomiting, measured via a 10-point visual analogue scale BID and antiemetic medication requirements up to 72 hours following catheter insertion. First assessment will be conducted when patient is awake and able to follow commands following extubation, second assessment will be conducted at the first intervention dose following first assessment, and ongoing assessments will be conducted at approximately every 12 hours thereafter.
- Quality of Recovery-15 Scale administered 24-96 hours post-surgery

*Visit P1: Postoperative Follow-Up: 6 weeks  $\pm$  2 weeks post surgery (Phone-Call Visits)*

- PROMIS 29 score
- Opioid requirements post-discharge as assessed by prescriptions provided at time of discharge and during post-discharge follow-up visit using both patient health record and direct patient recounting

*Visit P2: Postoperative Follow-Up: 3 months  $\pm$  4 weeks post surgery (Phone-Call Visit)*

- PROMIS 29 score
- McGill Pain Questionnaire
- Opioid requirements post-discharge as assessed by prescriptions provided at time of discharge and during post-discharge follow-up visit using both patient health record and direct patient recounting

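### The primary-endpoint rule counts the whole day of catheter insertion, so as written it spans 72 + t hours (t = clock hour of insertion), and the SAP does not say that pre-insertion opioids are left out

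*Combined protocol and SAP*

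**What the plan says.** SAP 3.4.1 (Primary Analysis) names the endpoint as "cumulative postoperative opioid use measured as MMEs during the 72 hours following catheter insertion". It then explains the limit of the data: "Administered opioids are documented in the CRF on a daily basis; i.e., the date and time of each administered drug is not recorded". The date and time of catheter insertion, by contrast, are recorded.

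The total is therefore assembled from calendar days:

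- day 0: "The day of catheter administration", with no fraction and no exclusion;
- days 1 and 2: both in full;
- day 3: "A fraction of the third day following the day of catheter administration", equal to the clock hour of insertion divided by 24. The worked example has insertion at 09:00 and 40 MME on day 3, which contributes 15 MME.

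Other relevant places:

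- **Timing of the block.** Protocol synopsis, Study Intervention: "Catheters will be inserted into the superficial parasternal intercostal plane bilaterally under ultrasound guidance after skin closure".
- **Source of opioid data.** Protocol 5.2 (Hospitalization) collects postoperative opioid use from catheter insertion, "obtained via medication administration record (MAR").
- **Intraoperative opioids.** SAP 3.3.4: "Intraoperative MMEs will also be summarized". SAP 3.4.1 also enters them in the primary ANCOVA as a median split.
- **Secondary endpoint.** SAP 3.4.2 analyses opioid use until discharge by the same methods as the primary endpoint.

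**The concern.** The rule trims the end of the window by the time of insertion but does not trim the start. The endpoint begins at insertion; the first bullet begins at midnight. Catheters go in after skin closure, so any opioid given in theatre that day comes before the block, as does any dose between the end of surgery and insertion.

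Doses given before the block cannot respond to it. If they are in the day-0 total, the primary outcome carries variation unrelated to treatment, and power falls. Intraoperative MME would also sit both in the outcome and among its covariates. Opioid use until discharge starts at the same point and would inherit the problem. The MME scale makes this worth checking: at the protocol's factor of 0.2 per microgram of intravenous fentanyl, 10/0.2 = 50 micrograms already equals the 10 MME target difference.

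There is a smaller problem at the other end. The day-3 fraction divides by 24 hours even for a patient who died or left hospital that day, and so counts too little of that patient's use.

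**Working it through.** **1. Reproduce the plan's own figures.** SAP 3.4.1 example: (9/24) × 40 = 15 MME, as stated. SAP 2.2.2: difference 10, SD 25, two-sided 5%, power 90%. The two-sample t-test needs 132.3 per group, rounded up to the stated 133. With 340 randomized and 25% attrition, 170 × 0.75 = 127.5 per group remain, and power is 88.9%.

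**2. Length of the window.** Let t be the clock hour of insertion.

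- As written: 24 + 48 + t = 72 + t hours.
- If day 0 holds only post-insertion doses: (24 − t) + 48 + t = 72 hours for every t.

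| Insertion | As written | Excess over 72 h |
|---|---|---|
| 09:00 (SAP example) | 81 h | 12.5% |
| 13:00 | 85 h | 18.1% |
| 17:00 | 89 h | 23.6% |

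The day-3 fraction is thus correct only on the second reading. These are calendar hours; they do not show how much opioid was given in the extra time.

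**3. Cost if pre-insertion doses are in the day-0 total.** The documents give no SD for pre-insertion MME, so s below is an assumption. Take it as intraoperative MME, normally distributed and independent of post-insertion use, which has the planned SD of 25. The SAP's median split then removes 2/π of its variance:

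residual SD = √(25² + s²(1 − 2/π))

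Power is for a 10 MME difference at 127.5 per group, two-sided 5%.

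| Assumed s | Residual SD | Power |
|---|---|---|
| 0 | 25.0 | 88.9% |
| 10 | 25.7 | 87% |
| 25 | 29.2 | 78% |
| 50 | 39.2 | 53% |

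**4. Day 3 for patients who leave or die that day.** Take insertion at 14:00 and discharge at 10:00 on day 3. The 72 hours end at 14:00, so every day-3 dose is inside the window, yet the rule counts 14/24 = 58% of them. Let H be the hours in hospital on day 3. Then t/H = 14/10 = 1.4 would over-count, whereas min(t, H)/H = 10/10 = 1 is right. With discharge at 20:00 the capped fraction is 14/20 = 0.70, against 14/24 = 0.58 under the rule.

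**The case against.** The strongest reply is that the rule works if the daily CRF entries are postoperative only. The endpoint is called postoperative, the estimand again limits it to MME in the 72 hours after insertion, and intraoperative MME is held as its own variable. Since catheters go in after skin closure, a postoperative day-0 total would cover roughly the 24 − t hours after insertion, and the rule would give about 72 hours. The t/24 fraction makes sense only on that reading, so it may well be the intended one.

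Most of this stands. A reader might infer from the first bullet that theatre opioids do enter the primary outcome. The documents do not establish that: the CRF is not among them, and neither the protocol nor the SAP says what the day-0 total contains. A delay between surgery and insertion is not documented either. Protocol 3.6 says study bags may go to the operating room or the ICU, but protocol 3.7 describes those who apply the intervention as operating room staff.

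The reply does not dispose of the point. Postoperative is not the same as after insertion, and insertion is where both documents start the clock. The bullets are the operative derivation of the primary outcome, and two programmers could follow them to different totals.

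**Conclusion.** The day-0 rule in SAP 3.4.1 departs from the endpoint that it is meant to derive. That much follows from the text: 72 + t hours as written, 81 hours in the SAP's example. The practical size depends on a fact that the documents do not give, namely the content of the CRF day-0 total.

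- If that total is postoperative only, the error is limited to doses between the end of surgery and insertion.
- If it includes intraoperative or other pre-insertion doses, precision is lost in the primary endpoint and in opioid use until discharge. The power figures of 87%, 78% and 53% are illustrations that rest on assumed SDs, independence and normality. They are not estimates for this trial.

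A reader might infer that the treatment comparison would be biased. It should not be: those doses precede study drug under randomization and blinding, so they add variance and leave the expected difference unchanged. Nor should one conclude that time to first opioid cannot be derived. The SAP's remark concerns the daily opioid record, and that endpoint may have its own field.

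The day-3 under-count is real arithmetic, but the documents do not show how many patients it affects. Because the rule determines the primary outcome, it should be settled before database lock.

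**What to change.** 1. Replace the first bullet of SAP 3.4.1 with: opioids given on day 0 after the recorded time of catheter insertion; intraoperative and other pre-insertion opioids are excluded. Apply the same start to opioid use until discharge in SAP 3.4.2.
2. Before lock, confirm what the CRF day-0 total contains. Subtract intraoperative MME only if that total includes it; otherwise the subtraction would itself create an error.
3. Where dose times for days 0 and 3 can be retrieved from the medication administration record, count the doses inside the exact 72 hours.
4. Where they cannot, keep the pro-rata rule but set the day-3 fraction to min(t, H)/H, with H the hours in hospital on day 3. A patient with H = 0 contributes nothing for that day.

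The cost is a wording change and a small change to the derivation. The record look-up covers two days per patient and is optional extra work. If the CRF total is already clean, steps 1 and 2 only put the intended rule in writing.

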### 3.5 Randomization Procedure

Randomization will be performed via a centralized, web-based platform that uses permuted blocks of varying sizes. Randomization will be stratified by site and patient sex. Dedicated unblinded individuals at each site who are responsible for preparing the assigned blinded bags of ropivacaine and saline will be provided with a randomization code list. Details on participant allocation and the randomization code lists will not be shared with the blinded study team members.

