## **7. Statistical Analysis and Sample Size Calculation**

For the primary analysis, we will perform linear regression, adjusted for sex (clinical stratification factor) and intraoperative opioid MME to assess the comparison between trial groups, with a P-value threshold of 0.05 being considered significant. If residuals indicate substantial violations of the linear regression assumptions, alternate methods will be attempted, such as analyzing log-transformed data, using bootstrap hypothesis testing or two-sample t-tests without equal variance. A modified intention-to-treat analysis will be employed, including only patients in whom a block catheter was placed, and a dose of study drug was administered. The time-to-event outcomes will be modelled simultaneously using a multistate framework. This approach will handle competing risks, such as death, and treat other non-fatal events, that could be related to each other, as intercurrent events. Sensitivity analyses using complete intention-to-treat and per protocol populations will also be conducted. Categorical data will be summarized by frequencies and percentages, and continuous variables by means and standard deviations (plus medians and interquartile ranges for non-symmetric data).

In order to detect a mean difference of 10 MMEs, assuming a standard deviation of 25 and an alpha value of 0.05, a sample size of 133 participants per group would be required to provide a power of 90%. Assuming an attrition rate of 25%, approximately 340 patients will need to be randomized for the primary modified intention-to-treat analysis.

Pre-specified subgroup analyses of the primary outcome include:

- Age
- Race/Ethnicity
- Sex/Gender
- Diabetes status
- BMI
- Type of operation
- Site

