### 2.2 Study Design

#### 2.2.1 Overview

EPOCH CardioLink-10 is a randomized, double-blinded, parallel-group, multicentre study of superficial parasternal intercostal plane blocks with 0.2% ropivacaine versus placebo with 0.9% normal saline administered via catheters in the SPIP placed under ultrasound guidance in patients undergoing cardiac surgery through a median sternotomy. Patients meeting inclusion

criteria who provide informed consent will be randomized in a 1:1 fashion into the intervention or control group. Based on the sample size calculation described in Section 2.2.2, approximately 340 participants will need to be randomized to detect important differences. This will be a multicentre trial at 4 sites in Canada, with usual institutional anesthetic and postoperative analgesia management being provided to all enrolled participants. Participants will be followed prospectively during hospitalization with regular assessments of postoperative pain and recovery, as well as during follow-up contacts at 6 weeks and 3-6 months following their operation.

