### 3.4.2 Secondary Efficacy Endpoints

Pain score during the 72 hours following catheter insertion will be analyzed by a mixed model for repeated measures (MMRM), with random effects for intercept and time, fixed effects for treatment, sex, and intraoperative MMEs (<median, ≥median), and an unstructured covariance matrix.

The analysis of cumulative postoperative opioid use measured as MMEs from catheter insertion until discharge from hospital will be by the same methods as for the primary efficacy endpoint, including the joint model sensitivity analysis.

The analysis of incidence of delirium during the 72 hours following catheter insertion will be by logistic regression with fixed effects for treatment group, sex, and intraoperative MME (<median, ≥median). The treatment odds ratio (OR) and associated 95% confidence interval will be provided.

The analysis of Quality of Recovery-15 Scale administered 24-96 hours post-surgery will be by the same methods as for the primary efficacy endpoint.

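### The primary ANCOVA omits site, a randomisation stratification factor, so its standard error is somewhat too large if site predicts opioid use; cutting intraoperative MME at the median loses further efficiency.

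*Combined protocol and SAP*

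**What the plan says.** Protocol 3.5 states: "Randomization will be stratified by site and patient sex". It uses a "centralized, web-based platform that uses permuted blocks of varying sizes". SAP 2.2.1 adds "This will be a multicentre trial at 4 sites in Canada", "with usual institutional anesthetic and postoperative analgesia management being provided to all enrolled participants".

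The primary model in SAP 3.4.1 is given as "The analysis of covariance (ANCOVA) model with a fixed effects for treatment group, sex, BMI and intraoperative MMEs", the last in two classes split at the median, with a separate variance per arm. It has no site term.

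Protocol section 7 describes the primary analysis as "linear regression, adjusted for sex (clinical stratification factor) and intraoperative opioid MME". It gives no cut-point for intraoperative MME and has no site term either.

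Site is in no SAP efficacy model. The pain, delirium and time-to-event models (SAP 3.4.2 and 3.4.3) adjust for sex and median-split intraoperative MME. MME to discharge and QoR-15 inherit the primary method. Site is a subgroup factor in protocol section 7, is missing from the subgroup list in SAP 3.4.4, and otherwise appears in the SAP only as a baseline descriptor. No reason is given for leaving out site or for the median cut.

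**The concern.** Blocked randomisation within site keeps the arms nearly balanced on site, so differences between sites hardly enter the treatment contrast. A model without site still counts those differences as residual noise. Its reported standard error then overstates how much the estimate really varies: the confidence interval is too wide and the test rejects too rarely. The endpoint is opioid consumption and analgesia is left to local practice, so a site effect is plausible.

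The median cut is a different matter. Intraoperative MME is not a design factor. It is settled before the first study dose, because catheters go in after skin closure, so it is a legitimate covariate. Reducing it to two classes discards some of what it explains, but the standard error remains honest for the model fitted.

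At stake is precision the trial has already paid for, not the validity of a positive result.

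**Working it through.** **1. The plan's own figure.** Inputs from SAP 2.2.2: difference 10 MME, SD 25, two-sided 5%, power 90%. Normal approximation: n = 2 × (1.960 + 1.282)² × 25² / 10² = 131.3, so 132 per group. The t-test calculation gives 133 with power 90.1%, which reproduces the stated figure. SD 25 carries no stated reduction for covariates. With 25% attrition, 340 × 0.75 = 255 patients, or m = 127.5 per arm. The unadjusted standard error is 25 × √(2/127.5) = 3.131.

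**2. Site.** Let s be the share of outcome variance explained by site. The documents do not give it; the range 0 to 20% is an assumption. Suppose blocks balance site at randomisation and a fraction d = 0.25 is then lost at random. That loss returns a share d of the site variance to the contrast. Without a site term:

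- reported SE = 3.131, because the site variance stays in the residual
- actual SE = 3.131 × √(1 − 0.75s)
- ratio = 1/√(1 − 0.75s)
- type I error = 2 × [1 − Φ(1.96 × ratio)]
- power without site = Φ[(10 − 1.96 × 3.131)/actual SE]
- power with site = Φ[10/(3.131 × √(1 − s)) − 1.96]

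| s | Actual SE | Reported/actual | Type I error | Power, no site | Power, with site |
|---|---|---|---|---|---|
| 0 | 3.131 | 1.000 | 5.0% | 89.1% | 89.1% |
| 5% | 3.072 | 1.019 | 4.6% | 89.6% | 90.6% |
| 10% | 3.011 | 1.040 | 4.2% | 90.0% | 92.0% |
| 20% | 2.887 | 1.085 | 3.4% | 91.0% | 94.6% |

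The power given up is 0, 1.0, 2.0 and about 3.7 points.

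A simulation of 340 patients randomised in permuted blocks by site and sex, with 25% random loss and 6,000 runs per scenario, agrees to within simulation error. The SE excess was about 1%, 3% to 5% and about 8% at s = 5%, 10% and 20%. Type I error was 4.8% to 4.9%, 4.0% to 4.3% and 3.1% to 3.6%.

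A second simulation had 266 patients, no loss, s = 20% and a correlation of 0.5 between intraoperative MME and the outcome. It checks the remedy. Without site the model reported 2.81 to 2.82 against an actual 2.47 to 2.52. With site it reported 2.46 against 2.46 to 2.50, and type I error returned to about 5%. This run used a common variance and no BMI term; neither BMI nor separate variances per arm replaces a site term.

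**3. Median cut.** A median split of a normal covariate keeps 2/π = 0.637 of its explained variance. With correlation ρ to the outcome (also not in the documents), the residual variance relative to a linear term is (1 − 0.637ρ²)/(1 − ρ²):

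- ρ = 0: 1.000, SE ratio 1.000
- ρ = 0.3: 0.943/0.910 = 1.036, SE ratio 1.018
- ρ = 0.5: 0.841/0.750 = 1.121, SE ratio 1.059

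Type I error is unaffected. The gain depends on the functional form. When intraoperative MME was simulated as log-normal, with the outcome linear in its logarithm, an untransformed linear term and the median split gave the same reported SE of 2.82, each with site in the model.

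**The case against.** The strongest case is that nothing planned is broken. The sample size assumes no covariate gain, the error is conservative, and the contrast is unbiased. Protocol and SAP agree in leaving site out, and the protocol's label for sex can be read as a deliberate choice to adjust for the clinical stratification factor and not the administrative one. Both key inputs are assumed. Local practice also governs anaesthesia, so intraoperative MME may already absorb part of any site effect.

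Much of this stands. The size of the loss cannot be taken from the documents, and the range must start at zero. Agreement between the documents shows consistency, but it gives no reason for stratifying on a factor and then ignoring it.

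A reader might infer more than the documents support:

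- **A larger site effect.** Assuming perfect site balance among those analysed gives SE excesses of 5% and 12%, and type I errors of 3.9% and 2.8%, at s = 10% and 20%. Block balance holds at randomisation. The mITT population and the plan's own 25% attrition weaken it.
- **A conservative test from the median cut.** That follows only from omitting a stratification factor.
- **An underpowered trial because of this model.** The 89.1% at s = 0 arises because 255 patients fall short of 266, whatever the covariates.
- **The same remedy everywhere.** For delirium ("The analysis of incidence of delirium during the 72 hours following catheter insertion will be by logistic regression") and the time-to-event endpoints, adding site changes the conditional odds or hazard ratio being estimated, and events may be sparse across four sites.

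**Conclusion.** The point holds as a modest, nearly free improvement in precision. The omission of site and the median cut are certain from the text; the size of their effect is not.

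For site, at an assumed variance share of 0% to 20% and 25% random loss, the reported SE is about 0% to 8% too large, type I error runs from 5% down to about 3.4%, and about 0 to 4 points of power are given up. If site explains nothing, nothing is lost. The median cut costs about 0% to 6% of the SE at correlations of 0 to 0.5 under a normal covariate, with a valid test throughout. The documents do not support a claim of bias, inflated false positives or a faulty sample-size calculation on this ground.

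**What to change.** Before unblinding, amend SAP 3.4.1 so that the primary ANCOVA contains treatment, site (four levels), sex, BMI and intraoperative MME as one continuous term whose form is fixed in advance, for example log(1+MME). A rule that picks the form after inspecting the skewness would not be a single pre-specified model. Make the same changes in the other continuous-endpoint models: MME to discharge, pain and QoR-15. Keep the median split for the subgroup display in SAP 3.4.4. If the sponsor prefers the present model, state the reason in the SAP.

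Adding site to the delirium and time-to-event models is optional. If it is done, say that the odds or hazard ratio is then conditional on site, and set out what happens if events are too few.

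Cost: SAP wording, minor programming, three degrees of freedom out of about 255 patients, and reliance on an assumed functional form for intraoperative MME. No new data are needed.
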